### Analysis and Reporting of Results

Baseline characteristics of all women enrolled in the study are documented and analysed in order to verify the absence of confounding differences in baseline variables between groups. Outcome comparisons for women will be analysed according to 'intention to treat'. Relative risks and 95% confidence intervals will be reported for the primary and secondary outcomes, and the number needed to treat to prevent one MRP will be calculated. A data management safety board will check the data at regular intervals.

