### Trial Entry

Eligible women will be identified in the labour ward at 20 minutes after delivery of the infant. The bladder will be catheterised, an intravenous canula will be inserted and normal saline solution will be started, CCT will be performed again and blood will be taken for cross-match and haemoglobin concentration. They will receive verbal and written information in Kiswahili about participation in the trial and will be asked to give their informed consent. The randomisation schedule uses balanced variable blocks; sealed envelopes containing both registration form and blinded study medication are present in the delivery room. Allocation will be in sequence of enrolment in each of the five labour wards. Each sealed envelop contains two identical capsules with either 800 microgram misoprostol or placebo. The patient, the maternal care providers and the researchers are all blinded to the allocation. Women will enter the study after giving their informed consent at 30 minutes following the delivery of the infant, at which time the envelope will be opened and the two capsules of study medication will be administered sublingually. Figure 1 depicts the flowchart for trial entry.

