### Sample Size

The primary endpoint of the study is manual removal of the placenta. For eligible women (with RP 30 minutes after delivery of the infant) the best estimate of MRP is 44% at 60 minutes post partum. Using 2:1 misoprostol to placebo randomisation, a sample size of 117 women will be able to show a 40% reduction in MRP (5% level of significance, two-tailed alpha, 80% power). Thus, 39 patients will receive placebo and 78 will receive misoprostol.

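### The baseline comparison is given a purpose it cannot serve: comparing measured variables in 39 versus 78 randomised women cannot verify that confounding is absent

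*Protocol article*

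**What the plan says.** In the protocol article, Analysis and Reporting of Results states that baseline characteristics of all enrolled women will be documented and "analysed in order to verify the absence of confounding differences in baseline variables between groups". It names no test, no threshold for a difference that matters, and no action if one is found.

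The same section plans an intention-to-treat analysis and says "Relative risks and 95% confidence intervals will be reported for the primary and secondary outcomes", with a number needed to treat for the primary outcome. Adjustment for covariates is not mentioned anywhere in the article.

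Trial Entry describes the allocation: "The randomisation schedule uses balanced variable blocks", "Allocation will be in sequence of enrolment in each of the five labour wards", and "The patient, the maternal care providers and the researchers are all blinded to the allocation". Active and placebo capsules are identical and come in sealed envelopes. Sample Size gives the arms as 39 placebo and 78 misoprostol.

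**The concern.** The fault lies in what the article states, not in what it leaves out. It treats the absence of confounding as something a look at the baseline data can establish. Three things are wrong with that.

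- Under the allocation described in Trial Entry, there is no systematic difference between arms to rule out. A test of baseline equality tests a hypothesis already known to be true.
- A comparison of measured variables is silent on unmeasured ones.
- At this size, a result that looks clean can coexist with an imbalance large enough to shift the relative risk.

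Two misreadings are at stake. A clean table may be taken as proof that the crude estimate needs no support. A chance difference may be taken as evidence that a sound randomised comparison is confounded. The article does not say what would follow in the second case.

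**Working it through.** **Inputs.** The arm sizes 39 and 78 are from Sample Size (39 + 78 = 117, ratio 2:1) and are taken as stated. Whether 117 suits the planned effect is a separate question and does not enter here. The planned effect is from the same section: "a sample size of 117 women will be able to show a 40% reduction in MRP". Three things are assumed, because the article does not give them: that the baseline analysis means two-sided tests at 5%, that 10 independent variables are compared (range 5 to 15), and the risks in step 3.

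**1. What would pass as absent.**
- Continuous variable: the smallest observed difference that reaches p < 0.05 is 1.96 × √(1/39 + 1/78) = 1.96 × 0.196 = 0.38 SD.
- Binary factor near 50%: 1.96 × √(0.25 × (1/39 + 1/78)) = 1.96 × 0.098 = 0.192, about 19 percentage points.

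Any smaller observed imbalance would be reported as no difference.

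**2. What would be flagged in a sound trial.** The chance of at least one p < 0.05 among k independent variables under correct randomisation is 1 − 0.95^k.

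| k (assumed) | chance of at least one flag |
|---|---|
| 5 | 23% |
| 10 | 40% |
| 15 | 54% |

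**3. Whether an unflagged imbalance can matter (illustration, all risks assumed).** Suppose a factor raises the risk of manual removal from 30% to 60%, and is present in 50% of placebo and 35% of misoprostol women.
- Baseline test: the pooled proportion is (0.50 × 39 + 0.35 × 78)/117 = 0.40. The standard error is √(0.40 × 0.60 × (1/39 + 1/78)) = 0.096. Then z = 0.15/0.096 = 1.56 and p is about 0.12, so the factor passes.
- Outcome with no drug effect: the placebo risk is 0.30 + 0.30 × 0.50 = 0.45 and the misoprostol risk is 0.30 + 0.30 × 0.35 = 0.405. The relative risk is 0.405/0.45 = 0.90.

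That is an apparent 10% reduction, a quarter of the planned 40%, from a factor the check would have cleared.

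**4. What data-driven adjustment would do to type I error, if it were done.** This was simulated under no treatment effect: 39 versus 78, five normal covariates, a linear outcome model, and 20,000 trials per setting (Monte Carlo standard error about 0.15 points, from √(0.05 × 0.95/20,000)).

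| Analysis | covariates explain 0% | 10% | 30% of outcome variance |
|---|---|---|---|
| Pre-specified adjustment | 4.8% | 5.1% | 5.1% |
| Adjust only for covariates that test as imbalanced | 4.9% | 4.8% | 4.3% |
| Smaller p of the unadjusted and imbalance-adjusted analyses | 5.2% | 5.4% | 5.7% |

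The shifts are small. The model is linear and the trial's endpoint is binary, so the table indicates size only.

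**The case against.** The best defence is that this is one loose phrase in a condensed article. The verb used may mean no more than tabulating by arm and inspecting, which is good practice. The only outcome analysis stated is an intention-to-treat relative risk, and the phrase does not alter it. A covariate strategy is normally left to the full protocol or the SAP, neither of which is shown. Much of this stands: a missing covariate list is no finding, and the figures for tests in steps 1 and 2 are conditional on tests being used.

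Three stronger readings are tempting and should not be made.

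- *That the choice between crude and adjusted estimates will be made after seeing the data.* The article mentions no adjustment and no consequence of a failed check. It leaves the matter open; it does not plan a data-driven choice.
- *That the error rate is materially distorted.* Step 4 shows that adjusting only for flagged covariates keeps type I error at or below nominal. Even picking the smaller p-value takes it only to 5.7%.
- *That the check has a certain power, for example 53%, to detect a real imbalance of 0.4 SD.* Randomisation rules out a real difference between the populations, so only the observed difference matters. An observed 0.4 SD gives z = 0.4/0.196 = 2.04 and is always flagged. An observed 0.3 SD gives z = 0.3/0.196 = 1.53 and never is.

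The defence does not rescue the stated purpose. Whether the table is tested or only inspected, it cannot verify that confounding is absent.

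**Conclusion.** The point holds in limited form and is minor. The stated aim of the baseline analysis is statistically invalid under the article's own allocation design, and at 39 versus 78 a clean comparison carries little reassurance. If tests are used, observed imbalances up to about 0.38 SD, or about 19 points for a binary factor near 50%, pass unnoticed. With an assumed 10 independent variables, at least one flag appears in 40% of sound trials.

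The stated intention-to-treat relative risk remains a valid comparison. What the wording risks is misinterpretation of the baseline table and an unplanned reaction to it.

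**What to change.** 1. **Reword the baseline sentence**, for example: *Baseline characteristics will be summarised by arm, without significance tests, to describe the women enrolled.* Drop the aim of verifying that confounding is absent.
2. **Stratify the primary relative risk by hospital**, for example by Mantel–Haenszel, because allocation runs within each of the five labour wards.
3. **Add one pre-specified supporting analysis** of the primary outcome, for example modified Poisson regression. Adjust it for haemoglobin and blood loss at entry, and report it whatever the observed balance. Trial Entry has blood taken for haemoglobin, and blood loss must be assessed to apply the exclusion criteria. Include gestational age only if it is recorded for every woman: women can qualify on the baby's weight instead, so the article does not establish that it is.

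The cost is a wording change and one extra model. No sample size, visit or measurement changes, except that gestational age would have to be confirmed as recorded before it is used.

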### Aims of the trial

The aims of this randomised, double blind, placebo-controlled trial is to assess if sublingual misoprostol reduces the need of Manual Removal of Placenta (MRP) and the amount of blood loss in women with RP in a low resource setting. The primary outcome variable is reduction in the incidence of MRP and the secondary outcome variable is the reduction in the number of units of packed cells administered.

The primary hypothesis of this randomised trial is that the administration of misoprostol to women with RP reduces the number of women who need MRP. The secondary hypothesis is that misoprostol reduces the amount of blood loss in women with RP, especially in those in whom the placenta is expelled by the intervention. Since measurement of blood loss during delivery is not always very reliable, we choose as secondary outcome variable both the measured amount of blood loss and the number of administered packed cells.

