### Exclusion criteria

Women with one of the following conditions will be excluded from entering the trial:

• Haemoglobin concentration less than 100 g/l (6.2 mmol/l)

• Blood loss more than 750 ml

• Pulse rate more than 120 beats per minute

• Diastolic blood pressure reduction after delivery more than 20 mmHg

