### Study Medication & Treatment Schedules

After administration of the study medication, the doctor or midwife will perform CCT every ten minutes to check if the placenta has separated from the uterine wall. Vaginal blood loss will be measured by weighing self absorbable mattresses. Blood loss exceeding 1500 ml will be considered as indication for emergency MRP. If the placenta is not expelled 30 minutes after the administration of the study medication, the patient will undergo MRP.

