### Study Endpoints

The primary study outcome is:

• Manual removal of the placenta.

The secondary outcomes are:

• Measured post partum blood loss,

• Number of units of blood administered,

• Adverse outcome for the woman, including side-effects from the study medication and number of emergency MRP needed.

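### Relative risk is the stated measure for the secondary outcomes, but it does not fit blood loss in ml or number of units transfused, and no outcome cut-point is given

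*Protocol article*

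**What the plan says.** Protocol article, Analysis and Reporting of Results: "Relative risks and 95% confidence intervals will be reported for the primary and secondary outcomes". The section names no other effect measure apart from the number needed to treat for manual removal of the placenta (MRP), and it makes no exception by type of outcome.

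Study Endpoints lists three secondary outcomes:

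- The first is an amount: "Measured post partum blood loss".
- The second is a count: "Number of units of blood administered".
- The third is a group of events, covering harms and urgent MRP.

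Aims of the trial describes the first two in the same way: "we choose as secondary outcome variable both the measured amount of blood loss and the number of administered packed cells". Study Medication & Treatment Schedules gives the method of measurement: "Vaginal blood loss will be measured by weighing self absorbable mattresses". The secondary hypothesis, also in Aims of the trial, is that misoprostol lowers the amount of blood lost.

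**The concern.** A relative risk compares two proportions, so each woman must either have the event or not. Millilitres of blood and units transfused supply no event until someone splits them, and the article defines no split. Taken at its word, the sentence leaves two options: dichotomise at a threshold that is not stated, or depart from the sentence.

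Dichotomising blood loss would replace a hypothesis about an amount with one about crossing a line. It would discard information in a trial of 117 women, and the size of the reported effect would depend on where the line was drawn. The Discussion ties wider availability of misoprostol to confirming effects on both MRP and blood loss, so the blood-loss result is meant to carry weight.

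**Working it through.** The plan contains no figure of its own on this point. The check is a comparison of outcome scale with stated measure, followed by two illustrations of size.

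**1. Scale against measure**

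| Outcome | Scale | Does a relative risk fit? |
|---|---|---|
| MRP (primary) | yes/no | Yes |
| Emergency MRP, each side effect | yes/no per woman | Yes |
| Measured blood loss | continuous (ml, weighed) | No |
| Units of blood | count per woman | Not as worded; only if reduced to any versus none |

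**2. Is an outcome cut-point stated anywhere?** Two blood-loss thresholds appear. "Blood loss more than 750 ml" is an exclusion criterion, and the abstract has the matching inclusion limit. "Blood loss exceeding 1500 ml will be considered as indication for emergency MRP" is a management trigger. Neither is presented as an outcome definition. No threshold for units appears.

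**3. Precision lost by a split (illustration).** Inputs: 39 placebo and 78 misoprostol, two-sided 5%, 80% power (Sample Size). The normal quantiles sum to 1.96 + 0.84 = 2.80.

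- Continuous analysis: detectable difference = 2.80 × SD × √(1/39 + 1/78) = 2.80 × 0.196 × SD = 0.55 SD.
- Median split of a normal outcome: information kept = 2/π = 0.64, equivalent to 0.64 × 117 ≈ 75 women. The detectable difference rises by √(π/2) = 1.25, to 0.55 × 1.25 ≈ 0.69 SD.

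The article gives no SD. For assumed values:

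| Assumed SD (ml) | Continuous: 0.55 SD (ml) | Median split: 0.69 SD (ml) |
|---|---|---|
| 300 | 165 | 207 |
| 500 | 275 | 345 |
| 700 | 385 | 483 |

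**4. Dependence on the cut (illustration).** Take the means that the Background quotes from the sulprostone trial, 1062 ml and 1450 ml (difference 388 ml). Assume log-normal blood loss with a coefficient of variation (CV) of 0.4, 0.6 or 0.8. With s² = ln(1 + CV²), the probability of exceeding a cut c is 1 − Φ{[ln c − (ln mean − s²/2)]/s}. The relative risk is the ratio of the two probabilities. Example for CV 0.6 and a 1000 ml cut: 0.433/0.653 = 0.66.

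| Cut (ml) | CV 0.4 | CV 0.6 | CV 0.8 |
|---|---|---|---|
| 500 | 0.97 | 0.91 | 0.87 |
| 1000 | 0.62 | 0.66 | 0.69 |
| 1500 | 0.35 | 0.50 | 0.58 |

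The difference in means is 388 ml in every cell. The cuts only show the sensitivity; none is suggested for use.

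**The case against.** The article condenses a full protocol and possibly an analysis plan that are not shown, and measures specific to each outcome are often left to those. The sentence may be shorthand for effect estimates with confidence intervals, and it does not forbid a mean difference. This has some force on how serious the issue is. It does not remove the point, because the article does name a measure and that measure does not fit two of the outcomes it covers.

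The mismatch is also limited in extent. Relative risk is right for MRP, emergency MRP and side effects. For transfusion, any versus none is a natural split, and the abstract's number of blood transfusions leans that way, although Aims of the trial and Study Endpoints specify units. The Background cites a 10% transfusion rate in women with retained placenta. If that held here, about 0.10 × 117 ≈ 12 women would be transfused, and any versus none would keep much of the usable information. Only blood loss has no natural split. All of this stands.

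A reader might infer that the cut-point would be picked after seeing the results. The article does not support that. It does not say when or by whom a threshold would be set, one may be fixed in a document not shown, and in a double-blind trial one could be set before unblinding. What can be said is that no threshold is stated here.

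Finally, the figures are generic. The 64% assumes a normal outcome split at its median, blood loss may well be skewed, and the means in step 4 come from a different drug given at 60 minutes. They show direction and rough scale only.

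**Conclusion.** The point holds in a limited form. The stated measure does not fit measured blood loss and, as worded, does not fit number of units. For blood loss, a relative risk would not answer the secondary hypothesis and would rest on a threshold the article does not give. This conclusion follows from the outcome definitions alone and needs no assumption about SD or distribution.

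The size of the consequence does need such assumptions. As an illustration, a median split moves the detectable difference from 0.55 to 0.69 SD, and the relative risk for one fixed difference in means can run from close to 1 to well below 0.6 depending on the cut. The issue is minor to moderate: the primary analysis, the sample size and the number needed to treat are untouched. It would go too far to say that relative risk is wrong for every secondary outcome, or that transfusion cannot be analysed as planned.

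**What to change.** Replace the sentence with one measure per outcome:

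- **MRP, emergency MRP, each side effect, any transfusion:** relative risk with 95% confidence interval.
- **Blood loss:** difference in mean ml with 95% confidence interval as the single main measure, using a bootstrap interval if the distribution is skewed.
- **Units of blood:** the relative risk of any transfusion, plus the difference in mean units with a bootstrap 95% confidence interval.

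Naming one main measure for blood loss matters, since a list of alternatives would leave open the choice that the change is meant to close. The cost is a few lines of wording and trivial extra analysis, with no new data and no change to treatment or follow-up. One limit should be accepted: if transfusion is as rare as the cited 10%, about 4 of 39 placebo women would be transfused (0.10 × 39 = 3.9), and the comparison of mean units will be imprecise whatever method is used.

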## Discussion

This is a protocol for RCT assessing the efficacy of sublingual misoprostol in women with a RP 30 minutes after delivery of the infant. The trial is conducted in a low-resource setting in order to establish if misoprostol treatment of RP reduces maternal morbidity associated with retained placenta in such a setting. This study is partially carried out in an environment where communication is difficult and where people have little experience with conducting research. During the research period we have to anticipate unforeseen difficulties like breakdown of equipment, loss of data or study medication and other unpredictable events.

When the hypotheses of the study, that misoprostol reduces the amount of MRP and blood loss, is confirmed, it should have consequences for the basic obstetrical care in rural health centres in developing countries. Misoprostol should then be made available to all health facilities and staff should be trained in administering the drugs correctly.
